## Abstract

**Introduction::**

Alzheimer disease (AD) is one of the most common diseases among the older adults. Currently, various nonpharmacological interventions are used for the treatment of AD. Such as reminiscence therapy is being widely used in Western countries. However, it is often used as an empirical application in China; the evidence-based efficacy of reminiscence therapy in AD patients remains to be determined. Therefore, the aim of this research is to assess the effectives of reminiscence therapy for Chinese elderly.

**Methods and analysis::**

This is a randomized parallel-design controlled trial. Mild and moderate AD patients who are in the Beijing Geriatric Hospital, China will be randomized into control and intervention groups (n = 45 for each group). For the intervention group, along with conventional drug therapy, participants will be exposed to a reminiscence therapy of 35 to 45 minutes, 2 times/wk for 12 consecutive weeks. Patients in the control group will undergo conventional drug therapy only. The primary outcome measure will be the differences in Alzheimer disease Assessment Scale-Cognitive Section Score. The secondary outcome measures will be the differences in the Cornell scale for depression in dementia, Neuropsychiatric Inventory score, and Barthel Index scores at baseline, at 4 and 12 weeks of treatment, and 12 weeks after treatment.

**Ethics and dissemination::**

The protocols have been approved by the ethics committee of Beijing Geriatric Hospital of China (approval no. 2015-010). Findings will be disseminated through presentation at scientific conferences and in academic journals.

**Trial registration::**

Chinese Clinical Trial Registry identifier ChiCTR-INR-16009505.

## Introduction

1

Alzheimer disease (AD) has been recognized as a progressive neurodegenerative disease with the common clinical manifestations of cognitive loss, problems with language, disorientation, loss of motivation, inability to perform self care, and the other neuropsychiatric and behavioral issues.^[1,2]^ Moreover, AD is a major cause of dementia, which is reported to account for approximately 60% to 70% of dementia cases.^[2]^ In developing countries such as China, evidence from epidemiological studies suggested that AD has become the fourth leading cause of death in the elderly, surpassed only by heart disease, cancer, and cerebrovascular disease.^[3]^ Therefore, AD has become a serious cause for the morbidity and mortality of the elderly in both developed and developing countries.

In contrast to the growing burden of AD-related health problems, effective strategies for the prevention and treatment of AD are rare. It has been indicated that patients suffering from AD are vulnerable to abnormalies in behavioral and psychological symptoms, such as depression, irritability, agitation, aggression, and delusions during the overall course of the disease.^[4]^ Accordingly, large numbers of prescriptions for antipsychotic and antidepressant drugs are dispensed to control the behavioral and psychological symptoms in patients with AD. However, the overall benefits of these medications are still under debate, because these antipsychotic and antidepressants drugs have the potential to cause serious side effects, such as metabolic disorders and stroke related mortality.^[5]^ On the contrary, increasing evidence suggests that nonpharmacological treatment for dementia associated with AD and other diseases may be optimal for the relieving of the physical and psychological symptoms, and more importantly, do not have serious adverse effects.^[6]^ Currently, various nonpharmacological treatments are used for the treatment of AD-related dementia, including behavioral intervention, music therapy, multisensory stimulation therapy, and reminiscence therapy,^[7]^ of which, reminiscence therapy is suggested to be of great potential.^[8]^ According to the definition from the American Psychological Association, reminiscence therapy is defined as the use of life histories—written, oral, or both to improve psychological well-being.^[9]^ Since the first performance of reminiscence therapy in 1963 by Butler, reminiscence therapy has now been applied in patients with chronic conditions, depression, and dementia from Western countries, Japan, Taiwan, and other regions of the world.^[10–18]^ Results of some pilot clinical trials have indicated the efficacy of reminiscence therapy for the improvement of cognitive function and overall quality of life, particularly the emotional function and overall happiness in these patients.^[19–24]^ However, in developing countries like China, reminiscence therapy is performed based on the judgment of the physician, and the evidence-based efficacy of reminiscence therapy in these patients remains to be determined. Therefore, we designed this randomized parallel-design controlled trial to evaluate the efficacy of reminiscence therapy on the cognitive, emotional, behavioral and psychological symptoms, as well as daily living ability of patients with AD. Results of our study may provide primary scientific evidence for the using of reminiscence therapy in AD-related dementia in China.

## Main objective

2

This study aims to assess the effects of reminiscence therapy on cognitive, emotional, behavioral, and psychological symptoms, daily living ability, and other aspects in patients with mild and moderate AD in addition to conventional drug treatment.

## Methods/design

3

### Study design

3.1

This randomized parallel-design controlled trial will be conducted in the Beijing Geriatric Hospital of China. A total of 90 patients with AD will be recruited and randomized into 2 groups: intervention and control group (n = 45 per group). Random number sequences will be generated by a statistician using SAS software, and sealed envelopes will be used for randomization. The statistician who randomly assigned the participants will not be responsible for the enrollment of subjects, and another independent statistician will be responsible for uncovering at the end of the trial. In the intervention group, along with conventional drug therapy, the patients will be subjected to reminiscence therapy for 35 to 45 minutes each time, and 2 times/wk for 12 consecutive weeks. The patients in the control group will undergo conventional drug therapy. The primary outcome will be changes in Alzheimer Disease Assessment Scale-Cognitive section (ADAS-Cog) scores in patients from each group, and the secondary outcomes are the changes of Cornell scale for depression in dementia (CSDD), Neuropsychiatric Inventory score (NPI), and Barthel Index (BI) scores. Evaluation will be performed before treatment, at 4 and 12 weeks of treatment, and 12 weeks after treatment.

### Study participants

3.2

Patients with mild-to-moderate AD from Beijing Geriatric Hospital, China.

### Inclusion criteria

3.3

Patients presenting with all of the following criteria will be considered for study inclusion.Men and women aged 65 to 89 years.Diagnosis of probable or possible AD based on the National Institute of Neurological and Communicative Disorders and Stroke and the Alzheimer's Disease and Related Disorders Association criteria.^[25]^Mild to moderate stage of dementia based on the clinical dementia rating score between 1.0 and 2.0.Informed consent provided by the patient and/or their legal guardian.

### Exclusion criteria

3.4

Patients with any of the following conditions will be excluded from this study.Diagnosis of cognitive impairment caused by vascular dementia, Lewy body dementia, frontotemporal dementia, Parkinson disease dementia, and other diseases except AD.Severe hearing loss.Serious communication barrier.Comorbidities of acute infection, trauma, myocardial infarction, and other emergencies.

### Withdrawal criteria

3.5

Patients who meet either of the following criteria will be withdrawn from this study.Complications that affect efficacy judgments or onset of disease that may affect outcomes.Use of other therapies to increase the speed of recovery.

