### Group assignment

3.8

Patients will be randomized into control and intervention groups, and the randomization concealment will be achieved by using the sealed envelope. A code will be written on each envelope. When participants meeting the inclusion criteria are included in the trial, they will be assigned a number. The envelope with the corresponding number will be opened, and the participant will be assigned to a group indicated in the envelope. The treatment protocol for each participant will be determined by a random sequence generated by computer. Patients and the outcome evaluators will be blinded to the group assignment.

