#### Sample size calculation

5.1.1

We used a power of 1 – β = 0.90, with a significance level of α = 0.05. The difference in ADAS-Cog scores was used as a primary outcome between the 2 groups after treatment. Given μ_α_ = 0.05, μ_β_ = 0.10, standard deviation (σ) = 15, and tolerance error (δ) = 10, we calculated a final effective sample size for n_1_ = n_2_ of approximately 33 per group using the sample size estimation formula.Secondary outcome required sample size: The secondary outcomes were evaluated by CDSS, NPI, and BI, respectively. According to the previous literature data, the required samples were calculated in 32 cases, 28 cases, and 39 cases for each group, respectively.According to the above data, the maximum value of 39 cases for the required sample size. If we assume a patient loss rate of 15%, we will require n_1_ = n_2_ = 45 patients per group. Therefore, we decided that a sample size of 45 patients per group will participate in the trial.

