#### Validity evaluation

5.1.2

A database will be established using EpiData 3.0 software. Statistical analyses will be performed using SPSS 13.0 software (SPSS, Chicago, IL). Continuous data will be expressed as the mean ± standard deviation. The data between groups will be compared using repeated measures analysis of variance. Qualitative data will be compared using the chi-square test. The significance level will be α = 0.05, and 2-sided tests will be used.

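### Section 3.5 withdraws randomised patients from the study, not only from the intervention, for outcome-related events after entry, which can bias the comparison of the arms

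*Protocol article*

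**What the plan says.** Section 3.4 of the protocol article lists who may not enter the trial. Section 3.5 is separate and governs patients already in it: "Patients who meet either of the following criteria will be withdrawn from this study". The two criteria are "Complications that affect efficacy judgments or onset of disease that may affect outcomes" and "Use of other therapies to increase the speed of recovery".

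Other sections that bear on the rule:

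- **Comparator (Abstract, Methods and analysis):** "Patients in the control group will undergo conventional drug therapy only". Under section 3.9 the intervention arm also meets in groups of 6 to 8, twice a week for 12 weeks, with a psychotherapist and 2 nurses.
- **Blinding (section 3.8):** "Patients and the outcome evaluators will be blinded to the group assignment".
- **Assessments (section 3.1):** "Evaluation will be performed before treatment, at 4 and 12 weeks of treatment, and 12 weeks after treatment".
- **Analysis (section 5.1.2):** "The data between groups will be compared using repeated measures analysis of variance".
- **Sample size (section 5.1.1):** the largest requirement, 39 per group, is raised to 45 per group for an assumed 15% loss. The ADAS-Cog inputs are an SD of 15 and a difference of 10.

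**The concern.** Randomisation makes the two groups comparable at entry. That comparability lasts only if patients are not then removed for reasons tied to how they are doing. Section 3.5 removes them on such grounds, and what ends is study participation, not merely the intervention. The first criterion selects patients because their scores are expected to be affected.

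The events could also differ in frequency, or in how often they are noticed, between the arms. Intervention patients are seen by staff twice a week in sessions that controls do not attend. Controls, or guardians acting for them, may have more reason to look for other therapies. The criteria carry no threshold, and the article does not name who applies them.

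If removal is related to outcome and unequal by arm, the patients who remain are no longer a fair comparison, and a difference can appear or disappear without any treatment effect. Scores that are never collected cannot be restored by choosing an analysis set later.

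**Working it through.** **1. The plan's own figure.** Inputs from section 5.1.1: 39 per group, 15% loss.

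- 39 × (1 + 0.15) = 44.85, rounded up to 45, the stated figure.
- 39 / (1 − 0.15) = 45.9, rounded up to 46, the usual form.

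The 45 is reproduced to within one patient. At 15% loss, 0.15 × 45 = 6.75, so about 7 patients per group could leave. The allowance replaces their number. It does nothing about which patients leave.

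**2. Bias when the worst-scoring patients are more likely to leave.** Let p be the proportion withdrawn in an arm, z the standard normal quantile at 1 − p, φ the normal density and ρ the correlation between the tendency to be withdrawn and the score. The mean of those who remain shifts by

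shift = ρ × SD × φ(z) / (1 − p)

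The bias in the comparison is the difference between the shifts in the two arms. The SD of 15 is the plan's. The withdrawal rates by arm and ρ are assumptions, since the article gives neither.

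*20% versus 10%:*
- φ(0.842)/0.80 = 0.280/0.80 = 0.350
- φ(1.282)/0.90 = 0.1755/0.90 = 0.195
- Difference 0.155; × 15 = 2.3; × 0.3 = 0.7 points; × 0.5 = 1.2 points

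*15% in one arm, none in the other, ρ = 1:*
- 15 × φ(1.036)/0.85 = 15 × 0.233/0.85 = 4.1 points

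**3. Simulation.** No true effect, SD 15, 45 per group, 20,000 trials, two-sided 5% t test at one time point on the patients who remain:

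| Withdrawn, arm A / arm B | ρ | Bias (points) | Type I error |
|---|---|---|---|
| 15% / 15% | 0.5 | about 0 | 4.7% |
| 20% / 10% | 0 | about 0 | 5.0% |
| 20% / 10% | 0.3 | 0.7 | 5.5% |
| 20% / 10% | 0.5 | 1.2 | 6.4% |
| 25% / 5% | 0.3 | 1.4 | 6.7% |
| 25% / 5% | 0.5 | 2.4 | 10.7% |
| 25% / 5% | 0.8 | 3.8 | 22.4% |

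Swapping the arms reverses the sign. If more poorly scoring controls are removed, the intervention looks worse than it is. If more poorly scoring intervention patients are removed, it looks better.

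The simulation is simpler than the planned repeated measures analysis, so it illustrates the mechanism and does not predict this trial's bias.

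**The case against.** **The link to arm is not in the text.** This stands. Section 3.5 ties withdrawal to outcome, and nothing in the article ties it to arm. Unequal withdrawal is an inference from the add-on design. A reader might infer that the rule certainly biases the result; the documents do not support that, and the table shows two cases in which the bias is about zero.

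**Nobody is named as deciding on withdrawal.** This stands too. A reader might infer that staff who know the allocation make the decision. The article does not say so, and section 3.8 states that patients and outcome evaluators are blinded. What remains is that no blinded decision is specified, and attendance at group sessions cannot be hidden from those who attend.

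**The 15% in section 5.1.1 is a general loss rate for both arms.** Correct. Placing all of it in one arm, with perfect correlation, is not the plan's assumption. The 4.1 points (41% of the 10-point design difference) must not be read as an expected bias.

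**An analysis plan may settle the analysis set and missing data.** It may, and their absence from a condensed article is no fault. Nothing says that scores taken before withdrawal are discarded, so an analysis of all observed scores could recover part of the information under stated assumptions. Classical repeated measures analysis of variance, which needs every visit, would not. Neither approach supplies the scores after the event, which the protocol itself stops collecting on a plain reading of section 3.5.

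**Follow-up may be impossible after some events.** True for some complications. This limits how complete follow-up can be; it does not justify ending assessment for everyone who meets a criterion.

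**Conclusion.** The concern holds as a fault in a stated rule, not as a missing detail. Mandatory withdrawal from the study on outcome-related grounds after randomisation can bias the comparison of the arms, and the 15% enlargement protects the numbers only.

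Size and direction cannot be known from the article. Moderately unequal withdrawal (20% versus 10%, correlation 0.3 to 0.5) gives about 0.7 to 1.2 ADAS-Cog points, or 7% to 12% of the 10-point design difference, with type I error of about 5.5% to 6.4%. Larger effects need strongly unequal withdrawal, such as 25% versus 5%. The bound of 4.1 points needs withdrawal in one arm only and perfect correlation. All of this rests on assumed rates and correlations, no true effect, and analysis of remaining patients only.

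Section 8.1 reports that recruitment is ongoing, so scores not collected under the present wording will stay missing.

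**What to change.** Re-word section 3.5 to separate stopping the intervention from leaving the study:

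- Record complications, new disease and use of other therapies as intercurrent events that do not end study participation.
- Continue the scheduled ADAS-Cog, CSDD, NPI and BI assessments where feasible, unless consent is withdrawn.
- Make the primary analysis all randomised patients in their assigned arm, with a method that uses all available scores, including those of patients with missed visits.
- Report the numbers and reasons by arm, and keep an analysis that excludes post-event scores as a sensitivity analysis only.

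Whether a patient continues the intervention stays with the clinicians.

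The cost is a short amendment, a few more assessments at visits already in the schedule, and possibly a less favourable effect estimate. No new sample size is needed for this change.

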### Recruitment

3.6

Outpatients and inpatients in the Dementia Unit will be recruited by dementia specialists. Potential participants will be able to contact the project manager via telephone and email.

### Baseline assessment

3.7

The baseline information that will be collected is shown in Table 1 (Additional file 2).

**Table 1 T1:**

Baseline characteristics of included patients.

### Group assignment

3.8

Patients will be randomized into control and intervention groups, and the randomization concealment will be achieved by using the sealed envelope. A code will be written on each envelope. When participants meeting the inclusion criteria are included in the trial, they will be assigned a number. The envelope with the corresponding number will be opened, and the participant will be assigned to a group indicated in the envelope. The treatment protocol for each participant will be determined by a random sequence generated by computer. Patients and the outcome evaluators will be blinded to the group assignment.


### Evaluation of efficacy

3.10

The reminiscence therapy's efficacy will be evaluated by 2 attending physicians from the Dementia Unit using a specially developed assessment manual before treatment, at 4 and 12 weeks of treatment, and 12 weeks after treatment.

### Primary outcome measure

3.11

The primary outcome is defined as the difference in ADAS-Cog scores before treatment, at 4 and 12 weeks of treatment, and 12 weeks after treatment. The ADAS-Cog, developed by Rosen et al,^[26]^ is a scale to assess cognitive function of patients with mild to moderate AD, and examines multiple cognitive domains including memory, language, praxis, and orientation. The ADAS-Cog has been well applied in trials of symptomatic treatments for mild-to-moderate AD, and its reliability and detection effectiveness have been confirmed to be acceptable by many clinical studies.^[27–29]^ Overall, it is widely used as an outcome measure in clinical trials that evaluate the cognitive changes of AD.^[30,31]^

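### The primary outcome spans four assessment times with none named as primary, the trial is sized on one between-group difference, and the planned ANOVA does not say which term or visit decides

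*Protocol article*

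**What the plan says.** Four places in the protocol article bear on the primary comparison.

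- Section 3.11 (Primary outcome measure): "The primary outcome is defined as the difference in ADAS-Cog scores before treatment, at 4 and 12 weeks of treatment", with the follow-up visit added as the fourth time. No time is singled out, and the text does not say between what the difference is taken.
- Section 3.1 (Study design): "The primary outcome will be changes in Alzheimer Disease Assessment Scale-Cognitive section (ADAS-Cog) scores in patients from each group". No time point is attached. The schedule follows: "Evaluation will be performed before treatment, at 4 and 12 weeks of treatment, and 12 weeks after treatment".
- Section 5.1.1 (Sample size calculation): "The difference in ADAS-Cog scores was used as a primary outcome between the 2 groups after treatment". The inputs are one difference and one standard deviation: "standard deviation (σ) = 15, and tolerance error (δ) = 10".
- Section 5.1.2 (Validity evaluation) compares the groups by repeated measures analysis of variance and adds: "The significance level will be α = 0.05, and 2-sided tests will be used". It does not say whether the group term, the group-by-time term or a contrast at one visit is decisive.

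The abstract lists the same schedule and names no primary time either.

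**The concern.** The section that defines the primary outcome and the section that sizes the trial describe different things. One covers a four-time profile that includes baseline, where a randomized comparison carries no information on efficacy. The other is a single contrast after treatment. The analysis section does not bridge them, because a two-group repeated measures ANOVA gives more than one test that could be called the result.

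Two things are at stake. If the deciding term or visit is picked once the results are known, the nominal 0.05 no longer describes the chance of a false claim. And if the group main effect is taken as the result, it estimates a different and smaller quantity than the difference used for sizing.

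**Working it through.** **Inputs from section 5.1.1:** difference δ = 10, SD σ = 15, α = 0.05, power 0.90, 33 per group stated for ADAS-Cog, 39 evaluable per group driving the trial size, 45 per group randomized. **From section 5.1.2:** two-sided tests. **From section 3.1:** four assessments, three of them after baseline. **Assumed:** the between-visit correlation ρ, which the article does not give, compound symmetry, and σ = 15 as the SD of the score at each visit.

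**1. The plan's own figure.** For two means, n = 2(z_α + z_β)²σ²/δ².
- Two-sided, power 0.90: 2 × (1.960 + 1.282)² × 225/100 = 47.3, so 48 per group.
- One-sided, power 0.90: 2 × (1.645 + 1.282)² × 2.25 = 38.5, so 39.
- The stated 33 appears only with one-sided α and power 0.85.

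So 33 does not follow from the stated inputs. That is a separate matter. What counts here is that the calculation uses one between-group difference at one time.

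**2. Power for the sized contrast at one visit, 39 per group.** SE = 15 × √(2/39) = 3.40; 10/3.40 = 2.94; power = Φ(2.94 − 1.96) = 0.84.

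**3. Power of the group main effect if all four times in section 3.11 enter the model.** Suppose there is a 10-point effect at each of the three later visits and none at baseline.
- Averaged effect: (0 + 10 + 10 + 10)/4 = 7.5.
- Variance of a patient's mean over four visits: σ²(1 + 3ρ)/4.
- ρ = 0.5: variance 140.6, SE = √(140.6 × 2/39) = 2.69, ratio 2.79, power 0.80.
- ρ = 0.8: variance 191.25, SE = √(191.25 × 2/39) = 3.13, ratio 2.39, power 0.67.

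If the effect were present at week 12 only, the averaged effect would be 10/4 = 2.5 and power about 0.13 to 0.15 (ρ = 0.8 to 0.5).

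**4. False-positive rate of the planned ANOVA.** This used 20,000 simulated null trials with 45 per arm and four times.

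| ρ | Group term | Group × time term | Either |
|---|---|---|---|
| 0.5 | 0.049 | 0.053 | 0.098 |
| 0.8 | 0.051 | 0.051 | 0.099 |

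Each term alone holds its level. Letting either count gives about 0.10, in line with 1 − 0.95² = 0.0975.

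**5. False-positive rate if any of three post-baseline visits counted at 0.05.** This is not a rule in the plan; it shows how far an open choice could go. Independent tests give 1 − 0.95³ = 0.143. Simulation of three equally correlated z-tests (2,000,000 draws) gives:

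| ρ | 0 | 0.5 | 0.7 | 0.8 | 0.9 |
|---|---|---|---|---|---|
| Rate | 0.143 | 0.125 | 0.109 | 0.099 | 0.084 |

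**The case against.** A reader might infer that the trial may claim success at any of three visits at 0.05 each. The article does not say that. Section 5.1.2 plans one between-group repeated measures ANOVA, which is a recognised way to handle several visits in one model, and a single pre-named omnibus term holds about 0.05. The 0.08 to 0.14 range therefore describes what an open choice would permit, not the error rate of the plan.

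A reader might also take the wording of section 3.1 to allow a claim on within-group change. That reading does not survive sections 5.1.1 and 5.1.2, both of which speak of a comparison between the groups.

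It can be said, too, that after treatment in section 5.1.1 most naturally means the end of the 12-week course, since the follow-up visit is always labelled separately. That is fair and weakens the ambiguity, but the phrase still does not name a visit, and section 3.11 still does not single one out.

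Finally, the choice of model term is often left to an analysis plan, and a whole-profile endpoint tested by one named term would be legitimate. This would answer a mere silence. It does not answer a primary outcome section that defines something other than what the sample size section sized. The power loss in step 3 applies to the group main effect with baseline included. It does not carry over to the group-by-time term, but that term tests any divergence between profiles and does not show at which visit the groups differ.

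**Conclusion.** The point holds as a mismatch between endpoint, sizing and analysis. No primary time is named, the four-time definition does not match the single sized difference, and the deciding ANOVA term or visit is open. No inflated error rate is planned. The exposure from a choice made after the data are seen is about 0.10 over two ANOVA terms, or about 0.08 to 0.14 over three visits for assumed correlations from 0.9 to 0.

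If the group main effect over all four times were the test, it would not address the sized contrast: a 10-point effect is diluted to 7.5, and power with 39 per group is about 0.67 to 0.80 (assumed ρ 0.8 to 0.5) against 0.84 at one visit. These power figures rest on compound symmetry, σ = 15 at every visit and a constant effect after baseline.

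**What to change.** Name one primary contrast: the between-group difference in ADAS-Cog change from baseline to week 12, the end of treatment, tested once at two-sided 0.05. State in section 5.1.2 the model contrast that tests it, for example the week-12 group contrast adjusted for baseline. Changing only the outcome wording would leave an omnibus ANOVA that does not test the named endpoint. Make week 4 and the follow-up visit secondary, and use the same definition in the abstract and in sections 3.1, 3.11, 5.1.1 and 5.1.2.

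The cost is a wording amendment. The article reports recruitment as ongoing, so it should be made before outcome data are seen by group. The small downside is that a difference seen only at week 4 or at follow-up becomes supportive evidence. The amendment does not settle the sample size: on the stated two-sided inputs a single contrast needs 48 evaluable per group, or 48/0.85 = 56.5, so 57, with 15% loss.
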